## 2. STUDY DESIGN

|             |                                                                                                                                                |                       |
|-------------|------------------------------------------------------------------------------------------------------------------------------------------------|-----------------------|
|             | Clinical Study Protocol                                                                                                                 |                       |
|             | Title: Measuring the Clinical Utility of Aegis's Chronic Disease Management Test among VillageMD Providers: A CPV® Randomized Controlled Trial |                       |
| Supersedes: | Document Number:                                                                                                                               |                       |
|             | Effective Date:                                                                                                                                | Page: 15 of 25 |

The study is an extension of QURE 3's patient simulation-based randomized-controlled study design which recruited a representative national sample of physicians. This QURE Village study will select a targeted and inclusive group of primary care providers in VillageMD clinics and assign them to either the control or the intervention group. All providers will then care for simulated patients via CPVs®.

Providers in both groups will complete, in random order, three CPV® patient simulations to determine their current practice when assessing patients facing medication non-adherence and DDIs. Cases will be identical across the intervention and control arms. Cases are interactive and are presented on an online platform that is accessible via unique weblinks and any internet-connected computer.

After the initial set of CPVs® are completed, intervention group providers will receive educational materials describing the clinical validation and use cases of the CDMT. The education materials are an orientation to the test, its use, and sample results directed to the participants who will adopt the CDMT (e.g., introduction slide deck, fact sheet, and/or case studies).

After receiving the CDMT education materials, intervention group providers will be asked to complete another set of CPVs®, this time, they'll be able to access the CDMT and its results and use it to diagnose and treat their patient. Control group providers will neither access the CDMT educational material nor be able to use its results in their routine care for their simulated patient.

## 2.1 Study Instruments

There are two data collection instruments: 1) the provider questionnaire; and 2) the CPV® simulated patient cases.

The online provider questionnaire consists of 10-15 questions to better understand provider demographics, training and practice environment. It will be administered once, upon enrollment into the study.

The CPV® cases will be designed to simulate typical patients with chronic cardiometabolic conditions and polypharmacy. In each case, providers will care for the simulated patient by indicating their preferred course of action to work- up, assess, and manage these patients. Providers will complete the cases in random order to cancel out any learning effects (which are known to be small), and only the intervention group will receive CDMT results at the appropriate point in each round 2 CPV® case whether they select it or not. All told, nine cases

|             |                                                                                                                                                |                       |
|-------------|------------------------------------------------------------------------------------------------------------------------------------------------|-----------------------|
|             | Clinical Study Protocol                                                                                                                 |                       |
|             | Title: Measuring the Clinical Utility of Aegis's Chronic Disease Management Test among VillageMD Providers: A CPV® Randomized Controlled Trial |                       |
| Supersedes: | Document Number:                                                                                                                               |                       |
|             | Effective Date:                                                                                                                                | Page: 16 of 25 |

will be developed, and any given provider will randomly be assigned to two rounds of three cases. Intervention will occur between the two rounds.

CPV® vignettes will be designed based on a 3 x 3 matrix of chronic cardiometabolic diseases and common drivers for non-adherence and potential drug-drug interactions.

|               | Variant A:
Not at goal
Test confirms
medication non-
adherence, no
DDI | Variant B:
Not at goal
Therapeutic
failure due to DDI
and/or Patient at
Risk for ADE | Variant C:
Not at goal, DDI
suspected
Test indicates adherence
to medications as
prescribed, no DDI |
|---------------|----------------------------------------------------------------------------------------------|------------------------------------------------------------------------------------------------------------|---------------------------------------------------------------------------------------------------------------------------|
| COPD   | Case 1A                                                                                      | Case 1B                                                                                                    | Case 1C                                                                                                                   |
| HF/AF  | Case 2A                                                                                      | Case 2B                                                                                                    | Case 2C                                                                                                                   |
| DM/HTN | Case 3A                                                                                      | Case 3B                                                                                                    | Case 3C                                                                                                                   |

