## Sample Size

The study will recruit 166 providers (83 per arm), with an expected sample size of 75 participants in each arm accounting for an estimated 10% attrition.

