## 8. STATISTICAL ANALYSIS

### a. Study Hypotheses

1. Provider participants at baseline will not recognize that patients do not meet therapeutic goals due to medication non-adherence and show high levels of unwarranted variation in their work-up, recognition, and management of medication non-adherence in patients with more than one chronic cardiometabolic conditions and associated polypharmacy using in the CPV® patient simulations.
2. Providers will not recognize that patients do not meet therapeutic goals due to DDI and show high levels of unwarranted variation in their work-up, recognition, and management of medication non-adherence in patients with more than one chronic cardiometabolic conditions and associated polypharmacy using in the CPV® patient simulations.
3. The intervention group, those who receive educational materials about the CDMT and CDMT results in their round 2 patient, will improve their quality of care and have less practice variation when caring for their CPV® patients with more than one chronic cardiometabolic conditions and associated polypharmacy, as measured by management decisions to recognize and/or manage medication non-adherence, DDI, and associated co-morbidities.
4. The additional information from the CDMT will result in better distinction between medication non-adherence and DDI and lead to better overall care including reduction in over-use of invasive diagnostic work-up and treatment, and a reduction in cost in a subset of patients. The associated cost savings, particularly for those patients will come from obviating high-cost workup, avoidance of unneeded subspecialty referrals, increased diagnosis and treatment of drug-drug interactions and/or reducing the frequency or number of medical interventions ordered.
5. Of the nine simulated cases that will focus on patients with multiple chronic cardiometabolic conditions and polypharmacy, there will be a subset of use cases where the CDMT demonstrates greater utility.
6. Providers with access to the education materials and CDMT will diagnose

|             |                                                                                                                                                |                       |
|-------------|------------------------------------------------------------------------------------------------------------------------------------------------|-----------------------|

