- Intervention status (exposure to intervention)

We will control for all potential confounders, including:

- Age
- Gender
- Years in practice
- Practice location
- Type of location (urban/suburban vs. rural)
- Weekly hours in clinical practice
- Number of providers in practice
- Avg. type of coverage of patients (Medicare, Medicaid, commercial, etc.)
- Participation in care quality incentive programs
- Percentage of patients that have chronic cardiometabolic disease

We will model CPV® scores as a continuous outcome variable in a multiple linear regression model, which controls for all potential confounders listed above.

Our regression model is as follows, where CPV® is the score for each provider and INTERV indicates intervention group and CASE indicates the order in which the provider took the case (first, second, third, fourth).

|             |                                                                                                                                                |                       |
|-------------|------------------------------------------------------------------------------------------------------------------------------------------------|-----------------------|
|             | Clinical Study Protocol                                                                                                                 |                       |
|             | Title: Measuring the Clinical Utility of Aegis’s Chronic Disease Management Test among VillageMD Providers: A CPV® Randomized Controlled Trial |                       |
| Supersedes: | Document Number:                                                                                                                               |                       |
|             | Effective Date:                                                                                                                                | Page: 23 of 25 |

$$Y_{it} = \text{CPV}^{\circledR} \text{ score of provider } i, \text{ at time } t$$

$$Y_{it} \sim \text{Normal}(\mu_{ijt}, \sigma^2)$$

$$\mu_{ijt} = \beta_0 + \beta_1 \text{CASE} + \beta_2 \text{INTERV} + \beta_3 \text{CASE} \times \text{INTERV} + \text{provider-practice variables}$$

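### The printed models have no term for which case or variant was seen, so case difficulty stays in the error and the use-case difference cannot be estimated from them

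*Protocol*

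**What the plan says.** Section 2.1 describes the pool and the draw. "CPV® vignettes will be designed based on a 3 x 3 matrix", with COPD, HF/AF and DM/HTN as rows and three causes as columns: confirmed non-adherence (A), drug-drug interaction (B), and adherent without interaction (C). Of these nine, "any given provider will randomly be assigned to two rounds of three cases". No rule is given for spreading variants or diseases over a round. Section 2 adds: "Cases will be identical across the intervention and control arms".

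Section 8.b (Longitudinal Data Analysis) prints the model for the CPV score: an intercept, CASE, INTERV, CASE x INTERV, and provider and practice variables. It defines the first of these terms: "CASE indicates the order in which the provider took the case". The list of positions that follows stops at the fourth, although each provider takes six cases. The logistic model has CASE, INTERV, TIME x INTERV and the same covariates. Neither model has a term for case, variant or disease.

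The use-case comparison is Objective 4 (Section 3). It is listed among both the primary and the secondary outcome variables in Section 8.b. Hypothesis 5 in Section 8.a expects that "there will be a subset of use cases where the CDMT demonstrates greater utility".

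**The concern.** A provider's round 1 and round 2 scores come from different cases. If some cases are harder than others, part of each provider's change reflects which cases were drawn. The analyst knows which case produced each score, so this noise could be removed, yet the printed models leave it in.

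The use-case question has a separate problem. A model without variant, or its interaction with round and arm, has no coefficient that answers Objective 4. Hypothesis 5 has no stated test or criterion. Some case will always rank highest, so ranking alone could not refute it.

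**Working it through.** **The plan's own figure.** The synopsis (Sample Size) says: "The study will recruit 166 providers (83 per arm), with an expected sample size of 75 participants in each arm". The loss it allows for is 10%. Check: 83 x 0.9 = 74.7, about 75. (75/0.9 = 83.3, which rounds up to 84; the difference is trivial.) The attrition step reproduces. I use 75 per arm, 150 in all.

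**Error inflation.** Let S² be the between-case variance of difficulty over the nine cases (divisor 8), and w² the residual variance of one score within a provider. Neither is in the document. Take six distinct cases, three per round, drawn without restriction.

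- Variance of a round's mean difficulty: (S²/3)(1 - 3/9) = (2/9)S².
- Covariance between the two rounds' means: -S²/9.
- Variance of the difficulty difference: 2 x (2/9)S² + 2 x S²/9 = (2/3)S².
- Residual variance of the change: w²/3 + w²/3 = (2/3)w².
- Inflation of the change-score variance: 1 + S²/w².

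To show what this means, suppose a contrast has 80% power at 75 per arm (two-sided 5%) without case variance. This is an illustration, not a figure from the plan.

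| S²/w² (assumed) | SE multiplier | Power, from 80% | Per arm to regain 80%: 75 x (1 + S²/w²) |
|---|---|---|---|
| 0.10 | 1.05 | 76% | 83 |
| 0.25 | 1.12 | 71% | 94 |
| 0.50 | 1.22 | 63% | 113 |
| 1.00 | 1.41 | 51% | 150 |

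The expected difficulty difference is the same in both arms, so the arm contrast stays centred on the true value.

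**Coverage of variants if the draw is unrestricted (assumption).** There are C(9,3) = 84 possible round 1 sets and C(6,3) = 20 round 2 sets for each, so 1,680 splits.

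- All three variants in a given round: 27/84 = 32.1%.
- A given variant absent from a given round: 20/84 = 23.8%, so present in round 2 for 76.2%.
- A given variant in both rounds: (45/84)(0.8) + (18/84)(0.5) = 45/84 = 53.6%. The other 46.4% (about 70 of 150) have no pre-post contrast of their own for it.
- All three variants in both rounds: (27/84)(8/20) = 12.9% (about 19 of 150).
- Some variant never seen: 3 x 20/1,680 = 3.6% (about 5 of 150).

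If cases could repeat across rounds, the third and fourth figures become (64/84)² = 58.0% in both rounds and (27/84)² = 10.3%.

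**What a restricted draw would give.** A triplet with one case per variant, each in a different disease row, can be formed in 3! = 6 ways. Each has two disjoint partners for the other round, giving 6 x 2 = 12 ordered sequences. Every provider then sees A, B and C in both rounds: 100% against 12.9%.

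**The case against.** Several points on the other side have force.

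- **Balance is not excluded.** Three cases per round from a three-by-three grid is compatible with a restricted random draw, and the allocation list may be specified elsewhere. This stands: the coverage percentages hold only for an unrestricted draw.
- **The analysis plan may add terms.** Interaction terms are ordinary SAP content, and the synopsis (Data Analysis) speaks of fixed effects without saying which. This explains how the gap might be closed. However, Section 8.b prints specific equations, and those equations contain no case or variant effect.
- **The loss may be small.** At a variance ratio of 0.10 it is about 5% on the standard error. This stands: the documents cannot settle the size.
- **A balanced draw has a drawback.** A provider who notices that every round holds one of each type could guess the last case by elimination. This is a reason to treat the restricted draw as secondary to the case term.

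Three stronger readings are tempting, and the documents do not support them. A reader might infer that many providers contribute nothing to the use-case comparison. In fact about 76% see a given variant in round 2 and inform the between-arm comparison, only 3.6% never see some variant, and a pooled regression also uses one-round observations. A reader might infer that random case assignment contradicts the statement that cases are identical across arms. That statement fits a pool common to both arms. Finally, a reader might infer that the largest of nine case effects will be selected and reported, with the optimism that brings. The protocol prescribes no such selection, and its outcome lists refer to three use-case types.

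**Conclusion.** The point holds for the models as printed. CASE records order, the order list covers four of six cases, and neither equation can separate case difficulty from error or estimate the treatment difference by use-case type. The consequence for the overall arm comparison is lost precision; an inference of bias is not supported, since cases are drawn at random from the same pool in both arms.

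The 5% to 41% range rests on the assumed variance ratios of 0.10 to 1.0 and applies to the linear score model with six distinct cases per provider. The figures of 46% without an own pre-post contrast and 13% with all three variants in both rounds rest on an unrestricted draw, which the protocol neither states nor rules out. The absence of any variant term for Objective 4 depends on neither assumption.

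**What to change.** 1. Add a nine-level case-identity effect to the linear and logistic models in Section 8.b. This removes additive difficulty variance and is worthwhile even if the assignment is left as it is. It uses 8 degrees of freedom out of 150 x 6 = 900 expected scores.
2. Assess Objective 4 with one test of variant x round x INTERV, with its lower-order terms in the model: (3 - 1)(2 - 1)(2 - 1) = 2 df. Show per-case estimates descriptively only, and tie Hypothesis 5 to this test.
3. State the assignment rule. Preferably, each round holds one case of each variant in different disease rows, using the 12 ordered sequences balanced across arms. The differences between variants and between diseases then cancel in the change score by design.
4. Extend the order list in the definition of CASE to six positions, and give case order and case identity different names.

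The cost is a revised assignment list on the online platform and a few model terms, with no extra cases or providers. The small downside of item 3 is that the last case's type can be guessed by elimination.

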## 2.2 Study Interventions

Intervention-arm providers will receive two interventions:

- Educational materials
  - All intervention group providers will first receive educational materials (e.g., a slide deck, webinar, fact sheet and/or case studies) on the CDMT.
- CDMT results
  - All intervention group providers will receive CDMT results at the appropriate point in each of the round 2 CPV® cases whether they select it or not.

## 3. STUDY OBJECTIVES

This study will test the improvement in quality of provider care decisions concerning medication non-adherence among patients with chronic cardiometabolic conditions using a well-validated patient-simulation based measurement approach, CPVs®, to assess the following:

- (1) To measure the variation in clinical decisions among practicing VillageMD primary care providers in the assessment, recognition, and adjustment of treatment due to medication non-adherence and DDI in patients with chronic cardiometabolic diseases.
- (2) To determine whether education about the Chronic Disease Management Test and provision of Chronic Disease Management Test results (i.e., the intervention) improves the quality of care, as measured by evidence-based management decisions to recognize and manage medication non-adherence including DDIs and the chronic cardiometabolic

|             |                                                                                                                                                |                       |
|-------------|------------------------------------------------------------------------------------------------------------------------------------------------|-----------------------|
|             | Clinical Study Protocol                                                                                                                 |                       |
|             | Title: Measuring the Clinical Utility of Aegis's Chronic Disease Management Test among VillageMD Providers: A CPV® Randomized Controlled Trial |                       |
| Supersedes: | Document Number:                                                                                                                               |                       |
|             | Effective Date:                                                                                                                                | Page: 17 of 25 |

conditions for which these medications are prescribed.

- (3) To model whether receiving Chronic Disease Management Test results leads to higher-value and/or lower-cost care decisions, including avoidance of invasive diagnostic tests or interventions, reduction of unneeded specialist referrals, increased diagnosis and treatment of drug-drug interactions, or care decisions that are expected to reduce overall costs (e.g., appropriate and safe medication prescription that will reduce risk of cardiovascular morbidity and mortality).
- (4) To determine whether the Chronic Disease Management Test results differentially impact the quality of care for different patient types (use cases).
- (5) To determine whether the targeted implementation of the Chronic Disease Management Test at VillageMD clinics could serve as a proof of concept for the remaining VillageMD primary care providers nationwide.

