## Study Design

The study is a prospective randomized cohort two-arm trial with six steps:

- 1) Enrollment: The study will enroll an estimated 166 practicing primary care providers, who practice at VillageMD clinics. An eligibility screener will be used to screen for eligibility (attached as Appendix A).
- 2) Provider survey: Once providers are enrolled in the study, they will be asked to complete an item questionnaire describing their practice, professional background and confidence in treating patients with cardiometabolic conditions.
- 3) Randomization: The 166 VillageMD providers will be randomized into two equally- sized arms: control group and intervention group.
- 4) CPVs® (First Round): Providers in both groups will complete three CPV® patient vignettes. Cases will be identical across the intervention and control arms. Cases are interactive and are presented on an online platform that is accessible via unique weblinks and any internet-connected computer.
- 5) Intervention education: For the intervention group, providers will receive educational materials describing the clinical validation and use cases of the Chronic Disease Management Test. The education materials are an orientation to the test, its use, the results directed to the participants that will adopt the CDMT (e.g., introduction slide deck, fact sheet, and/or case studies)
- 6) CPVs® (Second Round): All participating providers will then be asked to complete three additional CPV® patient simulations. The cases are again given to the doctors in a random order.

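### Objectives 3 and 4 and the additional-information hypothesis credit the CDMT results alone, but the two arms identify only the combined effect of education plus results

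*Protocol*

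**What the plan says.** The synopsis (Study Design) sets out two arms: "The 166 VillageMD providers will be randomized into two equally- sized arms: control group and intervention group". Section 2.2 states that "Intervention-arm providers will receive two interventions". The first is education: "All intervention group providers will first receive educational materials (e.g., a slide deck, webinar, fact sheet and/or case studies) on the CDMT". The second is the CDMT result, shown in every round 2 case whether or not the provider orders the test. Section 2 gives the other arm: "Control group providers will neither access the CDMT educational material nor be able to use its results". Section 8.b names one main explanatory variable, intervention status. The regression models carry it as INTERV, with an interaction by case order or time.

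The objectives and hypotheses differ in what they credit:

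- Objective 2 treats education and results together as the intervention.
- Section 8.a hypotheses 3 and 6 (synopsis hypotheses 4 and 7) also name both education and the test.
- Objective 3, on value and cost, names only the results: "To model whether receiving Chronic Disease Management Test results leads to higher-value and/or lower-cost care decisions".
- Objective 4, on use cases, does the same: "To determine whether the Chronic Disease Management Test results differentially impact the quality of care".
- Section 8.a hypothesis 4 (synopsis hypothesis 5) reads "The additional information from the CDMT will result in better distinction between medication non-adherence and DDI", and goes on to predict better care and lower cost.

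The synopsis repeats Objectives 3 and 4 in nearly the same words as Section 3.

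**The concern.** The two components reach the same people and are both in place for round 2, so the data cannot say which one changed a decision. Education is a plausible active ingredient on the protocol's own rationale. Section 1 describes the problem largely as one of recognition: clinicians seldom identify non-adherence, and physicians in the preceding study identified drug interactions in only 13% of the patients concerned. The materials describe the test's use cases and may include case studies. The vignettes in Section 2.1 are built on the same themes. Such material might lead a provider to consider non-adherence or an interaction without any result in hand, and it might do so more in some use cases than in others.

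At stake is what a positive trial may conclude. Section 1 says that data of this kind can influence coverage and reimbursement decisions. A cost saving or use-case difference reported as the effect of the test results would go beyond what the comparison shows.

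**Working it through.** **The plan's own figure.** The only numerical design figure is the sample size: 166 recruited, 83 per arm, about 75 per arm after 10% attrition. 83 × 0.9 = 74.7, which agrees. In the other direction, 75 / 0.9 = 83.3, or 84 per arm when rounded up, a trivial difference. The point here does not depend on sample size.

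**Identifiability, overall.** Inputs: two arms (synopsis, Study Design); both components given to all intervention providers (Section 2.2); neither given to controls (Section 2); intervention placed between the rounds (Section 2.1). Let E be the effect of education and R the effect of results.

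| Cell | Intercept | Round 2 | Arm | Education | Results |
|---|---|---|---|---|---|
| Control, round 1 | 1 | 0 | 0 | 0 | 0 |
| Control, round 2 | 1 | 1 | 0 | 0 | 0 |
| Intervention, round 1 | 1 | 0 | 1 | 0 | 0 |
| Intervention, round 2 | 1 | 1 | 1 | 1 | 1 |

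The last two columns are identical. There are 5 columns and the rank is 4. The difference-in-difference (intervention change minus control change) equals E + R. The round 1 baseline does not help, because both components are absent in round 1 and present in round 2.

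**Identifiability by use case (Objective 4).** With the three variants A, B and C and variant-specific effects, there are 15 columns and the rank is 12, so one combination is lost per variant. Within each variant only E + R is estimable. The contrast between variants A and B is

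(E_A + R_A) − (E_B + R_B) = (E_A − E_B) + (R_A − R_B).

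It equals the difference in results effects only if E_A = E_B, which the protocol does not state.

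**What would separate them.** Adding an education-only arm gives 6 columns and rank 6, so E and R both become estimable. The protocol has no such arm, no equivalent education for controls and no other contrast that does this.

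**Wording set against design.** Objective 2 and Section 8.a hypotheses 3 and 6 claim E + R, which the trial estimates. Objectives 3 and 4 and Section 8.a hypothesis 4 claim R, which it does not.

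**The case against.** The strongest reply is that Objectives 3 and 4 are shorthand. Objective 2 has just defined the intervention as both components, Section 2.2 lists both, the outcome measures in Section 3.1 compare arms, and the only exposure variable is intervention status. The education is an orientation to the test, close to instructions for use, so test plus orientation is the natural thing to deploy and a legitimate target. All of this stands, and it means the trial itself needs no repair. It does not rescue the wording. The protocol names both components in some objectives and hypotheses and only the results or their information in others, so a literal reader will take the difference as intended.

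A reader might infer that decisions made before the result appears in a round 2 case could serve as an education-only comparison. The protocol does not support this. It says only that results come at a suitable point in each case, and nothing about recording, locking or separately scoring earlier answers. In a provider's second and third round 2 cases, those decisions would also follow exposure to earlier results. Early and late decisions are likely to differ in kind too, work-up against management.

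A reader might also point to Section 6.3, which puts the education before the CPV cases without naming a round, and see an education-only round 1. The synopsis (Study Design), Section 2 and Section 2.1 all place it after round 1, and no planned analysis uses such a period.

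**Conclusion.** The point holds as a defect of attribution. Objectives 3 and 4 and the additional-information hypothesis claim an effect of the results that the two arms cannot isolate, and they depart from the protocol's own definition of the intervention in Objective 2. This is wrong as written, and a separate analysis plan could not recover the results effect from these two arms. It affects two of the five objectives and one hypothesis, each in both synopsis and body.

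Two stronger readings are not supported. One is that the trial is biased or invalid: the randomised comparison of the package with control is sound. The other is that the results effect is overstated by some stated factor. If education accounts for a share f of the package effect, attributing the whole to the results overstates them whenever f is above zero, but the documents give no information on f. Education may contribute nothing, part or all of the effect.

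The conclusion rests only on the allocation of the two components and on their timing between rounds.

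**What to change.** In both the synopsis and the body, reword Objectives 3 and 4 and the additional-information hypothesis (synopsis hypothesis 5, Section 8.a hypothesis 4) so that the effect is that of *education on the CDMT together with provision of its results*, matching Objective 2. State that the cost and use-case conclusions apply to that package. Changing only the body would leave the synopsis in conflict with it. The synopsis Summary and Section 1 also say that the results change decisions, and could be aligned in the same edit.

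The cost is a narrower claim. Arms, sample size, data collection and the package-versus-control analysis stay as they are.

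If a claim about the results alone is wanted, it needs an education-only arm or equivalent education for controls. For scale, assume two-sided 0.05, 80% power and a simple two-group comparison, none of which the protocol gives. Splitting 166 three ways with 10% attrition leaves 166 / 3 × 0.9 ≈ 50 per arm. The detectable difference, (1.960 + 0.842) × √(2/n), rises from 0.46 SD at n = 75 to 0.56 SD at n = 50. Rewording avoids that cost.
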